Our previous lab-based, proof-of-concept ABM intervention found reductions in pain intensity and pain interference from pre-ABM to post-ABM were associated with large effect sizes,^27^ although differences in methodology including delivery (online vs lab-based) and number of sessions warrant a more conservative estimate. On this basis, the study will recruit a minimum of 100 with 1:1:1:1 randomisation. This study is powered primarily to establish treatment efficacy for the primary outcome variable of pain interference by considering baseline and measures after session 10 between those randomised to an attentional modification arm and those randomised to a placebo arm. Randomisation should ensure baseline comparability on measures between these two groups, and a difference in beneficial outcomes between these groups will be modelled using a linear mixed model. For an assumed correlation of 0.7 between baseline and end of session 10 measures, a total of 40 per group (ie, 20 per randomised arm) would be needed to detect small to moderate standardised intervention differences (Cohen’s *d*=0.25) with at least 80% power (alpha=0.05, two-sided). The recruitment strategy includes a 20% oversampling to mitigate a loss of power from loss to follow-up.

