### Visual-probe tasks

The flow of visual-probe sessions is illustrated in figure 2. In total there will be eight linguistic and eight pictorial probe-classification visual-probe training tasks used in the study, each with different stimuli. A complete description of the stimuli including ratings of valence, arousal, pain intensity, written frequency and low-level features is provided in online supplementary material 1. To briefly summarise, each linguistic visual-probe task includes 32 threatening/neutral and 16 neutral/neutral word pairs. Each task includes eight threatening words from each of the following categories: sensory pain, affective pain, health threat and general threat. Each pictorial task includes 32 threatening/neutral and 16 neutral/neutral image pairs. Each task includes eight threatening images from the following categories: musculoskeletal pain, facial expressions of pain, health threat and general threat. A total of 384 trials are included in each task, with each stimuli pair presented four times for 500 ms and four times for 1250 ms. Within each exposure duration, each stimulus appears twice in the upper location of the screen and twice in the lower location.

10.1136/bmjopen-2019-030607.supp1Supplementary data

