For visual-probe data, and as per previous research,^19 27^ practice and incorrect trials will be removed prior to analyses. Box and whisker plots for overall data will be used to reveal overall outliers, which will be removed. Following this, mean response times will be computed for each participant, with any response >3 SD from their individual mean also removed as outliers. This process ensures extremely quick or slow responses do not unduly bias the results, which are typically removed when cleaning and screening visual-probe data in pain-related research (eg, refs 18 64–67). An attentional bias index will then be computed for each stimulus and presentation time condition using the following equation: (TuPl−TlPl)+(TlPu−TuPu)/2. Here T is the threatening stimulus, P is the probe, u is the upper position and l is the lower position. The attention capturing quality of threatening stimuli is measured by subtracting the mean probe classification time for congruent trials from the mean probe classification time of incongruent trials.^21^

Split-half reliability will be computed via a bootstrap procedure, by randomly splitting the total number of trials in two halves, such that each half has the same number of congruent and incongruent trials. Attentional bias scores will be computed for each half and the correlation between them calculated across participants. This procedure will be repeated 100 times, and an average split-half correlation computed.

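### The planned split-half figure is an uncorrected half-length correlation, possibly pooled over conditions, so it is not the reliability of the attentional bias index that is analysed

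*Protocol article*

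**What the plan says.** The procedure is in the protocol article, Quantitative analyses, in the paragraphs on visual-probe data. After error trials and outliers are removed, "An attentional bias index will then be computed for each stimulus and presentation time condition". Reliability is then defined in sequence:

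- The split: "Split-half reliability will be computed via a bootstrap procedure, by randomly splitting the total number of trials in two halves".
- The balance: "such that each half has the same number of congruent and incongruent trials".
- The statistic: "Attentional bias scores will be computed for each half and the correlation between them calculated across participants".
- The end point: "This procedure will be repeated 100 times, and an average split-half correlation computed".

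No step from half length to full length is given there or elsewhere in the article. On task length, the Visual-probe tasks section says "A total of 384 trials are included in each task".

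**The concern.** A correlation between two half-scores estimates the reliability of a score built from half the trials. Averaging over 100 random splits removes dependence on any one split, but every split is still half length, so the average carries the same length effect.

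There is also a mismatch in what is split. The index is defined by condition, while the split is described for the total number of trials. A reader cannot tell whether the correlation is computed within each condition or on scores pooled over conditions.

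What is at stake is the reading of mechanism. The Introduction reports four earlier studies of this training in chronic pain. Three found no evidence that attentional bias changed, and one did not record it. This trial reassesses bias at endline and at 6 months. If bias again appears unchanged, readers will ask whether the index could have shown a change, and the reliability figure is the planned evidence on that.

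**Working it through.** The article states no reliability value and no expected correlation, so there is no figure to reproduce. The check covers what the written procedure estimates.

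**Inputs from the article.** Each task has 48 stimulus pairs (32 threat/neutral, 16 neutral/neutral), each shown 8 times: 48 × 8 = 384 trials, of which 32 × 8 = 256 are threat/neutral. Each threat category has 8 stimuli, and each pair is shown 4 times per exposure duration. One duration therefore has 32 × 4 = 128 threat trials, and one category at one duration has 8 × 4 = 32. The planned sample is at least 100.

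**Assumptions.** The assessment task has the same trial counts as the training tasks, for which they are stated. Trials are homogeneous. The within-person trial SD is 150 ms. The range of r is left open.

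**Reading A: halves formed within one index.** Let T be the variance of true bias and E the error variance of the full-length index. A half-length score has error variance 2E. Full-length reliability is R = T/(T+E), and the half-score correlation is r = T/(T+2E). Hence r = R/(2−R), and conversely R = 2r/(1+r).

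| mean r | 2r/(1+r) | shortfall |
|---|---|---|
| 0.10 | 0.18 | 0.08 |
| 0.30 | 0.46 | 0.16 |
| 0.40 | 0.57 | 0.17 |
| 0.50 | 0.67 | 0.17 |
| 0.70 | 0.82 | 0.12 |
| 0.90 | 0.95 | 0.05 |

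The shortfall r(1−r)/(1+r) is largest, about 0.17, near r = 0.4. It is nil at r = 0. At r = −0.10 the formula gives −0.22, so it should not be applied to negative values.

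A simulation of the written procedure agrees (100 participants, halves balanced on congruency, 100 splits, 40 replicates per scenario):

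| true full-length reliability | mean r, 256 trials | corrected | mean r, 32 trials | corrected |
|---|---|---|---|---|
| 0.2 | 0.11 | 0.19 | 0.11 | 0.19 |
| 0.4 | 0.24 | 0.38 | 0.27 | 0.42 |
| 0.6 | 0.44 | 0.61 | 0.42 | 0.59 |
| 0.8 | 0.67 | 0.80 | 0.67 | 0.80 |

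With true reliability 0, the mean r and the corrected value were both close to 0.

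**Reading B: halves pooled over conditions.** Half of the 256 threat trials is 128.

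- For an index per duration (128 trials), the pooled half has the same length, so the uncorrected r is about right for that index.
- For an index per category and duration (32 trials), the pooled half is four times as long. If that index has reliability 0.10, the pooled half gives r = (4 × 0.10)/(1 + 3 × 0.10) = 0.4/1.3 = 0.31, which is too high. Stepping up gives 2 × 0.31/1.31 = 0.47, further from 0.10.

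The direction of the error therefore depends on a choice that the article leaves open. Adding the correction without changing the split could make matters worse.

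**The case against.** The strongest objection concerns direction. A reader might infer that the reported reliability must come out too low. The article does not support that. Under the pooled reading, which is the literal one, the value may be about right or too high. Under the within-condition reading, it is too low only if r is positive. This part of the objection stands, and the point is worded accordingly.

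A second objection is that the article is a condensed account and a detailed analysis plan is to follow. That plan may add the step. But the article does not simply leave reliability to later: it gives a full recipe from split to final statistic, and that recipe ends at the averaged correlation. The final statistic is accurately named a split-half correlation, but the sentence that introduces it calls it reliability.

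A third objection concerns consequences. A reader might infer that a correction for attenuation would be distorted, or that the Reliable Change Index is affected. Neither follows. No attenuation correction is planned, and the Reliable Change Index is for the primary and secondary outcomes, which do not include the bias index. The article also sets no reliability threshold for interpreting a null result.

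Finally, a reader can apply 2r/(1+r) to a published average. That is true only if the report says which trials were split.

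**Conclusion.** The point holds in limited form. As written, the procedure does not estimate the reliability of the index that is analysed. With within-condition halves and positive r, it understates that reliability by up to about 0.17 (for example, 0.30 reported against 0.46). With pooled halves, it describes a score as long as or longer than the analysed index and may overstate (0.31 against 0.10 in the 32-trial example).

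These sizes rest on parallel halves, homogeneous trials and, for the pooled case, the training-task trial counts carried over to the assessment task. Since no expected r is given, the actual error cannot be fixed in advance.

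The severity is minor. The figure enters no sample size, primary analysis or listed outcome. Its importance lies in whether an unchanged bias score is put down to the training or to the measure.

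**What to change.** Reword the reliability paragraph so that the random halves, balanced on congruency, are formed within each bias index actually analysed, at each assessment stage. For each, report the mean r over the 100 splits and, beside it, the Spearman-Brown value 2r/(1+r). Where the mean r is zero or negative, report it uncorrected. State the number of retained trials behind each value.

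The cost is a line or two of code and one or two sentences of text, with no new data. The small downsides are more values to report and less precise estimates by condition. At low r the correction also widens the sampling error: its slope is 2/(1+r)², which is 2/1.21 = 1.65 at r = 0.10.

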#### Qualitative analyses

Qualitative analysis will be used to detail participants’ experiences completing the iABMT intervention. Specifically, thematic analysis using inductive coding will be used to identify themes present in the data obtained from the semistructured interviews and the two open-ended questions included in the SOT questionnaire. Guidelines provided by Braun and Clarke^68^ will be followed. Following verbatim transcription of all interviews, initial codes will be generated. Potential themes and subthemes will then be identified from the initial coding, which subsequently will be reviewed and refined. The validity of the themes in relation to the data set will also be considered. Each theme and subtheme will then be named and defined, and a thematic map of the data finalised. Examples from the data will be illustrated for each theme and subtheme in the final report.

### Ethics and dissemination

The study protocol was registered with ClinicalTrials.gov, with a planned start date of September 2020 and a planned end date of September 2022. All data will remain confidential and stored on password-protected systems and databases. LifeGuide and iSurvey servers both use HTTPS (hypertext transfer protocol secure) connections for security purposes. All data will be anonymised prior to dissemination, and personally identifiable information not known to anyone other than the researchers. Participants may withdraw from the intervention at any point by contacting the researchers via email or telephone, or by simply opting not to log into their iABMT account for their scheduled sessions. Participants are also encouraged to contact the researchers should they experience any distress or discomfort completing the intervention. As per university policy, any adverse events, harms or complaints arising from participation in the intervention will be reported to the University of Southampton Research Governance Office. Findings will be published in the most relevant, high-impact, peer-reviewed journals and presented at relevant conferences. Lay reports will be written for interested pain charities and patient support groups.
